### Study/methods monitoring

This study was approved by the Medical University of SC Institutional Review Board (IRB) (Pro#00053520), the Charleston VA Research and Development Office; and the Department of Defense Human Research Protection Office. All participants receive verbal information about the study and a written and signed informed consent document is obtained for study purposes. Quarterly progress reports are submitted to the DoD and annual audits of the study are conducted by the MUSC IRB. Any adverse events are required to be reported to the IRB within 24 h and the study PI must respond in writing to the IRB regarding any needed change in procedures as applicable. MUSC IRB, the Charleston VA Research Office, and the Department of Defense Human Research Protection Office will monitor adverse events related to the study with regard to frequency, severity, and causality and will use these factors to determine whether the study should be terminated given the risk to benefit ratio. Any changes to the study protocol must be approved by MUSC IRB and The Department of Defense Human Research Protection Office; and updates to the ClinicalTrials.gov registry are made as applicable. A data monitoring committee was not established because the clinical trial is relatively small and poses minimal risk beyond usual care for the treatment of PTSD (i.e., usual care for PTSD is Prolonged Exposure). Although minimal risks with participation are anticipated, the Charleston VAMC will cover non-negligent harm associated with study participation and will provide alternative and/or additional medical services that may arise as consequence of study participation as part of the Veterans Health Administration.

### Data management

Data is compiled using codes in lieu of personal identifiers, and access to study data is limited to research personnel. Development of, and security oversight for, the electronic database for this study is performed by study personnel using a secure, web-based application to support data capture. The application provides: (1) an intuitive interface for data entry (with data validation); (2) audit trails for tracking data manipulation and export procedures; (3) automated export procedures for seamless data downloads to common statistical packages (SPSS, SAS, Stata); (4) procedures for importing data from external sources; and (5) advanced features, such as branching logic and calculated fields. Only de-identified data is entered into the electronic database. The data-entry management system is accessible from the Charleston VAMC. Although no Protected Health Information (PHI) is entered into the database, data system security is ensured by implementing multiple-layered firewalls and a network intrusion prevention system for identifying and blocking malicious network activity in real time. A hard-copy study log linking patient names with study ID numbers is kept in a locked cabinet in a secure room at the Charleston VAMC, and access to this log is limited to only approved few study personnel. The PI and Project Coordinator will have direct access to the dataset (interim and final) and will provide access to other Co-Investigators (Co-Is) on the study if requested once the dataset is finalized. A procedure for interim analyses was not included as part of the data management plan given the low anticipated risk to participants.

### Sample size calculation and power analyses

For the continuous longitudinal clinical, functional, and process outcomes for Primary Aims, with 35 subjects randomized to each intervention group, we will have 85% power to detect at least a 0.3 standardized (sd units) effect size between the two intervention groups assuming three time points, and an intra-class correlation no greater than 0.5; level of significance ≤ 0.05, two-tailed. A standardized effect size of 0.35 sd (Cohen’s *d*, “small” effect) is equivalent to a raw effect size of 2.8 raw scale units for the PCL (assuming pooled sd for post-treatment PCL scores is 8.1, from preliminary data). All participants randomized to condition and having completed a baseline assessment will be included in ITT analyses.

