**Methods/design:**

The study will include 70 veterans with PTSD treated at a Southeastern Veterans Affairs Medical Center (VAMC). All participants in the trial receive up to 12 sessions of PE. Participants are randomly assigned 1:1 to (1) volunteer at a local animal shelter or (2) volunteer at a community agency of their choice as part of their in-vivo exposure exercises for PE. Outcomes will be examined via standard clinical interviews, self-report questionnaires, and thematic interviews.

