### Study aims

RESCUE + PE will decrease emotional-numbing symptoms of PTSD relative to the PE control arm (CI + PE) primary outcomeRESCUE+PE will be feasible and acceptable to veteransTreatment engagement will be higher for the RESCUE + PE group relative to CI + PE group (i.e., higher treatment attendance rates (primary), homework completion rates, and treatment completion rates)Treatment recovery rates (as measured by PTSD diagnostic status yes/no; decreased PTSD symptom severity; and increased quality of life) will be higher for the RESCUE + PE group compared to the CI + PE group at post treatment and at 3-month follow-upParticipants randomized to RESCUE + PE will experience a decrease in PTSD numbing from pre to post treatment relative to those randomized to CI + PI

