### Analytic strategy

Data screening for violations of proposed statistical methods assumptions (normality of endogenous variables, linear relations among variables, no outliers, limited missing data/appropriate method for handling missing data) will include histograms, bivariate correlations, Q-Q plots, and other diagnostic methods. Processes associated with subject attrition will be examined to determine whether a missing-at-random assumption is defensible. Data will be analyzed to determine whether missing values are correlated with any baseline values and all relevant psychometric variables will be examined between groups at the baseline point of measurement to ensure adequate randomization. Given limitations of last-observation-carried-forward (LOCF), hierarchical linear models (HLM)/mixed models will be used for ITT analyses of primary and secondary outcome variables. Statistically significant treatment-related changes will be qualified with effect-size estimation and 95% confidence interval estimation.

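### The 85% power figure assumes three repeated measurements and cannot be carried over to attendance, a labelled-primary outcome with about 24% power at 0.3 SD; nor does 0.3 SD yield 85% for the repeated outcomes

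*Protocol article*

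**What the plan says.** The protocol article's section on sample size calculation and power analyses contains its only power figure. The sentence sets its scope and numbers as "For the continuous longitudinal clinical, functional, and process outcomes for Primary Aims, with 35 subjects randomized to each intervention group". For that design it then claims "85% power to detect at least a 0.3 standardized (sd units) effect size between the two intervention groups". The calculation takes three measurement occasions, an ICC capped at 0.5 and a two-sided 0.05 level. The next sentence uses a second effect size, 0.35 SD, which it calls Cohen's d.

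The study aims section labels emotional numbing as primary outcome. Under the engagement aim it lists "higher treatment attendance rates (primary), homework completion rates, and treatment completion rates". Prolonged Exposure runs to at most 12 weekly sessions.

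The analytic strategy states that "hierarchical linear models (HLM)/mixed models will be used for ITT analyses of primary and secondary outcome variables". The treatment effects section ties these models to pre-post continuous measures and assigns chi-square tests to dichotomous outcomes. The article does not define process outcomes or say how attendance is scored, and it gives no separate power figure for attendance.

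**The concern.** The power statement reaches process outcomes of the primary aims, and the only process measures named in the aims are the engagement ones. Attendance is the one marked primary among them. Yet the statement depends on features that an attendance rate does not naturally have: three measurement occasions and a correlation between them. Sessions attended out of a course is one bounded number per veteran, with no baseline value.

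Engagement is the trial's stated purpose. The discussion already concedes that negative findings will be harder to interpret. If a null attendance result were read against a nominal 85% power, it could be taken as evidence that the intervention does not improve attendance, when a design of this size would usually miss a 0.3 SD difference.

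**Working it through.** **Inputs.** From the sample size section: 35 per arm, effect 0.3 SD (0.35 SD also quoted), three time points, ICC up to 0.5, two-sided 0.05, stated power 85%. Assumption: attendance is scored as one value per veteran, and all 35 per arm contribute.

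**Method.** For a between-arm difference of d SD units, SE = sqrt(2V/35), where V is the variance of each veteran's summary relative to a single measurement. Power comes from the noncentral t distribution with 68 degrees of freedom and noncentrality d/SE.

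**Step 1: the plan's own figure.** For the average of three visits, V = (1 + 2 × ICC)/3. At ICC 0.5, V = 2/3, SE = sqrt(2 × 0.667/35) = 0.195 and noncentrality = 0.3/0.195 = 1.54. Power is about 33%, not 85%. Other readings at 0.3 SD (normal approximation):

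| Reading | Power |
|---|---|
| Three-visit average, ICC 0.5 | 34% (t: 33%) |
| Three-visit average, ICC 0 | 58% |
| Pre-post change, ICC 0.5 | 24% |
| Baseline-adjusted mean of two post values, ICC 0.5 | 43% |
| Baseline-adjusted mean of three post values, ICC 0.5 | 49% |
| Slope difference of 0.3 SD per visit, ICC 0.5 | 71% |

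Among the readings checked at ICC 0.5, two return the stated figure (86.7% normal, 85.8% t):
- 0.3 is Cohen's f. With two equal arms d = 2f = 0.6, so noncentrality = 0.6/0.195 = 3.07.
- V = (1 − ICC)/3 = 0.167. Then SE = sqrt(2 × 0.167/35) = 0.098, and noncentrality is again 3.07. This V leaves out the between-person variance.

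Neither is a 0.3 SD difference between groups as the sentence states it.

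**Step 2: one value per veteran.** V = 1, so SE = sqrt(2/35) = 0.239.

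| Effect | Noncentrality | Power |
|---|---|---|
| 0.30 SD | 1.26 | 23.6% (normal 24.1%) |
| 0.35 SD | 1.46 | 30.3% |
| 0.60 SD (f reading) | 2.51 | 69.7% |

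The effect detectable with 85% power is 0.73 SD (0.72 by the normal approximation). For the three-visit average at ICC 0.5 it is 0.73 × sqrt(2/3), about 0.59 SD. By the normal approximation, 85% power at 0.3 SD with one value per veteran would need about 200 per arm.

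**Step 3: splitting the gap.** On the stated SD-unit inputs, moving from three visits to one value lowers power from about 33% to about 24%, roughly 10 points. The rest of the distance from 85% is already there before attendance is considered.

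**Step 4: the model.** With one value per veteran there is no within-person level. A mixed model with randomised group as a fixed effect then reduces to an ordinary two-group comparison.

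**The case against.** The strongest reply is that the sentence limits itself to continuous longitudinal outcomes. A single bounded attendance rate is neither continuous in the usual sense nor longitudinal, so the 85% was never claimed for it. Process outcomes could mean something else: the assessment section lists weekly in-treatment forms, and one expectancy form is given at exactly three sessions. The primary label on attendance may only rank it among three engagement measures. Attendance could also be recorded session by session and analysed with a generalised mixed model, and scoring details may sit in a fuller plan.

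Much of this stands. A reader might infer that the article expressly claims 85% power for attendance; it does not, and bringing attendance under process outcomes is an inference. A reader might also infer that the stated mixed model cannot be fitted or that no workable test exists; that is too strong, because with one value the model becomes a two-group comparison.

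The reply does not rescue the figure. If attendance is outside the sentence, an outcome labelled primary has no applicable power figure, and the undefined wording invites the wrong reading. If attendance is scored by session, it is a repeated binary outcome over up to 12 sessions, and a continuous three-time-point calculation still does not describe it. The 85% also fails on its own terms for the outcomes it plainly covers, which is a matter of stated text and not of missing detail.

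**Conclusion.** The point holds in a limited form. The stated power cannot be carried over to attendance. With one value per veteran, 35 per arm and a two-sided 0.05 test, power is about 24% at 0.3 SD and 30% at 0.35 SD, and 85% power requires about 0.73 SD.

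It would be tempting to read the drop from 85% to 24% as the price of losing repeated measurements. The article's own inputs do not support that: the repeats account for about 10 points. The larger fault is that 85% does not follow from 0.3 SD even with three visits at ICC 0.5, where power is about 33% and the detectable effect about 0.59 SD. If 0.3 was meant as Cohen's f, one attendance value per veteran would have about 70% power at the corresponding d of 0.6.

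These figures assume one attendance value per veteran, complete data on 35 per arm and a t-type comparison of means. Fewer contributing veterans would lower them.

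**What to change.** In the sample size section:
- State that the 85% figure does not cover attendance.
- Add that 35 per arm gives 85% power for about 0.73 SD in sessions attended, taken as one value per veteran.
- Correct or justify the 85% for the repeatedly measured outcomes: name the contrast, the variance formula and whether 0.3 is d or f. If it is a 0.3 SD difference in a three-visit average at ICC 0.5, the power is about 33% and the detectable effect about 0.59 SD.

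In the analytic strategy, state that attendance is compared between arms per veteran with a 95% confidence interval, since the mixed model reduces to that comparison.

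The cost is a few sentences and a less favourable stated figure. No extra veterans or data are needed.

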## Background

Prolonged Exposure (PE) is considered an evidence-based treatment (EBT) for PTSD [1, 2] and has been widely disseminated throughout Department of Defense (DoD) and Veterans Affairs (VA) treatment facilities. Although up to 80% of patients demonstrate clinically meaningful improvement after completing an EBT for PTSD such as PE [1–3], a significant number of individuals do not initiate PTSD treatment or drop out of treatment prematurely (as high as 78% and 36% overall pooled dropout rates across studies) [4–7]. Given the wide-scale availability of PE and other EBTs for PTSD in VA and DoD treatment settings, and the robust effect sizes for treatment completers, there is a need for novel methods that can improve PTSD treatment engagement and decrease attrition.

One potential avenue for improving EBTs for PTSD is by targeting PTSD symptoms that may adversely impact treatment engagement early in the treatment process. Emotional numbing is part of the symptom profile of PTSD and consists of symptoms that reflect difficulties in experiencing positive emotions such as love and happiness, loss of interest in activities that were previously important or pleasurable, and feeling distant and cut off from others. In relation to PTSD and other psychiatric disorders, emotional numbing is also associated with apathy and low motivation [8, 9]. Together, these symptoms can limit an individual’s ability and willingness to engage in treatment [10, 11], particularly a treatment that encourages connecting emotionally with trauma-related material. Consistent with this, poor response to PE has been associated with blunted emotional reactivity to trauma cues early in therapy [12].

A promising mechanism for decreasing emotional numbing is through therapeutic human-animal interaction (HAI [13–15]). HAI refers to the purposeful and semistructured social pairing of a human with a domesticated animal for therapeutic purposes. A number of diverse studies have found that HAI can have positive effects on emotional and physical functioning, stress reactivity, and social functioning [16–18]; and among those with psychiatric symptoms, HAI interventions have been found to improve depression, anxiety, and PTSD [16, 19, 20]. Although promising, the HAI literature is tempered by methodological limitations, such as difficult-to-replicate study procedures, over-reliance on self-report measures, and lack of adequate controls/randomization (e.g., [18–20]).

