### Randomization procedures

Once eligibility is established, veterans are assigned 1:1 to one of the two treatment groups by the Project Coordinator using a web-based computer-generated randomization scheme. Once a veteran is randomized and attends the first session, they are entered into the study and included in the intent-to-treat (ITT) analysis. The post-treatment assessors (12- and 3-month assessors) will be blinded to condition. The Principal Investigator (PI) (for clinical oversight/supervision) and Project Coordinator (for randomization/regulatory reasons) will not be blinded to treatment condition. The study therapists likewise will not be blinded because discussion of volunteer assignments is part of the treatment protocol. It is not anticipated that the post-treatment assessors will need to be unblinded as this will be their only point of contact with the study participant. If the blind is accidentally broken, the Clinician Administered PTSD Scale (described below) will be reviewed by another team member for fidelity and evaluated against the PTSD Symptom Checklist (described below) which is self-report.

Inclusion criteria for the study are as follows: (1) *Diagnostic and Statistical Manual for Mental Disorders, version 5* (DSM-V) PTSD diagnosis (via the Clinician Administered PTSD Scale; CAPS [22];) stemming from a duty-related Criterion A event [23]; (2) male or female aged 18 to 64 years.

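### The stated 85% power for a 0.3 SD group difference does not follow from its own inputs: 35 per arm gives about 33% at ICC 0.5, and the raw-unit example uses a different effect (0.35 SD)

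*Protocol article*

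**What the plan says.** The section on sample size and power in the protocol article covers the continuous longitudinal outcomes for the primary aims. Its claim reads: "we will have 85% power to detect at least a 0.3 standardized (sd units) effect size between the two intervention groups". The arm size behind that claim is stated as "with 35 subjects randomized to each intervention group", and the randomization section confirms equal allocation: "veterans are assigned 1:1 to one of the two treatment groups". The repeated-measures conditions are "assuming three time points, and an intra-class correlation no greater than 0.5". The test itself is set at "level of significance ≤ 0.05, two-tailed".

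The next sentence changes the effect size. It takes 0.35 SD, calls it Cohen's d and small, and says that it "is equivalent to a raw effect size of 2.8 raw scale units for the PCL". The spread behind that conversion is given in brackets: "assuming pooled sd for post-treatment PCL scores is 8.1, from preliminary data". The section gives no formula or software and makes no explicit allowance for missing outcome data.

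**The concern.** A comparison of 35 with 35 rarely has high power for a standardized difference of 0.3. Three measurements per person help only modestly when they are correlated at 0.5, so 85% looked too high. The move from 0.3 to 0.35 in adjacent sentences also left it unclear which effect the trial is meant to detect.

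The paragraph supports the primary aim, the comparison of emotional numbing between arms. If it is wrong, readers will believe the trial can detect a small effect when it can reliably detect only one about twice that size. With 33% power, a true 0.3 SD difference would be missed about two times in three, and a null result could be taken as evidence against an effect the trial was never likely to see.

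**Working it through.** **Inputs**, all from the sample size section: n = 35 per arm (N = 70), m = 3 time points, ICC ρ up to 0.5, two-sided α = 0.05, effect 0.3 SD (0.35 SD in the conversion), PCL SD 8.1.

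**Step 1. The plan's figure from the plan's inputs.** In SD units, the mean of m equally correlated measurements has variance v = (1 + (m − 1)ρ)/m, and the group difference has SE = √(2v/n). At ρ = 0.5:

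- v = (1 + 2 × 0.5)/3 = 0.667
- SE = √(2 × 0.667/35) = 0.195
- noncentrality = 0.3/0.195 = 1.54
- power, noncentral t on 68 df = 32.9% (normal approximation 33.6%)

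The stated 85% is not reproduced.

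**Step 2. Can another permitted ICC rescue it?** In this formula a lower ICC raises power, so 0.5 is the worst case and 0 the best.

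| ICC | v | Power at 0.3 SD | Power at 0.35 SD |
|---|---|---|---|
| 0.5 | 0.667 | 32.9% | 42.4% |
| 0.25 | 0.500 | 41.7% | 53.3% |
| 0 | 0.333 | 57.3% | 70.5% |

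No entry reaches 85%.

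**Step 3. Can baseline adjustment rescue it?** With k follow-ups and correlation 0.5 throughout, v = (1 + (k − 1) × 0.5)/k − 0.25. Power at 0.3 SD is 29.8% for k = 1, 41.7% for k = 2 and 48.3% for k = 3. It does not.

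**Step 4. What does 35 per arm detect?** Solving the Step 1 calculation for 85% power at ρ = 0.5 gives 0.593 SD (0.585 by the normal approximation). On the PCL this is 0.593 × 8.1 = 4.8 points. As a measure of the gap, 85% power at 0.3 SD would need about 134 per arm under the same assumptions.

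**Step 5. Where might 85% come from?** The between-groups F test in a repeated-measures design has λ = N·m·f²/(1 + (m − 1)ρ), and for two equal groups f = d/2.

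- d = 0.3, so f = 0.15: λ = 70 × 3 × 0.0225/2 = 2.36, power 32.9%
- f = 0.30, so d = 0.6: λ = 70 × 3 × 0.09/2 = 9.45, power 85.8%

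Entering 0.3 as f reproduces the stated figure.

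**Step 6. The raw-unit conversion.** 0.35 × 8.1 = 2.84, which matches the stated 2.8. The effect that was powered gives 0.3 × 8.1 = 2.43. The multiplication is right, but it is applied to a different effect.

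**The case against.** The strongest objection is that the article does not name the tested contrast or formula, and a change or slope contrast would be plausible because the aims and treatment-effects sections speak of pre-post change and slopes. Some such routes come close. A variance of (1 − ICC)/m at 0.3 also gives 85.8%. A group-by-time F test gives 78% at f = 0.15 and 90% at f = 0.175, which brackets 85%. This part stands: a reader might infer that the f-for-d slip is proven, and it is not. The routes do not rescue the sentence, however. It describes a difference between two groups in SD units. Under the (1 − ICC)/m variance, power falls as the ICC falls (85.8% at 0.5, 57.3% at 0), so an upper limit on the ICC would be the wrong safeguard.

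A reader might also apply the treatment dropout cited in the Background ("as high as 78% and 36% overall pooled dropout rates across studies") and conclude that only 22 per arm remain. The documents do not support that. The figure is treatment dropout in other studies. Here, veterans who leave treatment are encouraged and paid to complete follow-up assessments, and the mixed model uses partial data.

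A further tempting reading is that the conversion uses the wrong outcome, the PCL total instead of a numbing score. The section refers only to PCL scores, the conversion is an illustration, and no SD for a numbing score is given.

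Two mitigating points are fair. The study overview already calls the work a pilot with initial efficacy testing, and the Discussion warns that negative findings will be harder to interpret. Neither mentions power, so neither corrects the figure.

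**Conclusion.** The point holds. On its stated inputs the design has about 33% power for a 0.3 SD group difference at ICC 0.5 and at most about 57% at ICC 0; for 0.35 SD the range is 42% to 71%. At ICC 0.5, 85% power corresponds to about 0.59 SD, or 4.8 PCL points, roughly twice the 2.4 to 2.8 points implied by the text. The mismatch between 0.3 and 0.35 is real but secondary.

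The result assumes equal correlation between time points, complete data and a group difference averaged over the three measurements. Single-occasion and baseline-adjusted versions also fall far short of 85%. Cohen's f as the source is the most likely explanation, but the conclusion does not depend on it. Missing outcome data would worsen the position by an amount the documents do not allow one to fix.

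**What to change.** Replace the power statement with one of this form: 35 per arm gives 85% power to detect a between-group difference of about 0.6 SD (Cohen's d; about 4.8 PCL points at SD 8.1), assuming complete data, three time points, ICC 0.5 and a two-sided 5% level. Use that single effect size throughout and remove 0.3, 0.35, 2.8 and the small-effect label. State the formula or software used. Add a sentence saying that missing outcome data would make the detectable effect larger, without equating 36% treatment dropout with 36% data loss.

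The cost is one reworded paragraph. Sample size, conduct and analysis stay as they are. The price is a less favourable statement of what the trial can detect.

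### The 85% power is tied to 0.3 SD and the 2.8 PCL points to 0.35 SD, and 35 per arm gives 85% power for neither

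*Protocol article*

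**What the plan says.** Everything at issue stands in the protocol article under Sample size calculation and power analyses. The power claim reads "we will have 85% power to detect at least a 0.3 standardized (sd units) effect size between the two intervention groups". Behind it stand 35 participants per arm, three measurements, an ICC capped at 0.5, and "level of significance ≤ 0.05, two-tailed". Randomization procedures confirms the allocation: "veterans are assigned 1:1 to one of the two treatment groups".

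The following sentence moves to another effect. It opens with "A standardized effect size of 0.35 sd", labels this a small Cohen's d, and says that it "is equivalent to a raw effect size of 2.8 raw scale units for the PCL". The SD used for the conversion is 8.1, taken from preliminary data on post-treatment scores. Nothing in the section connects 0.3 with 0.35. This is the only power statement in the article, and it is offered for the continuous longitudinal outcomes of the primary aims as a group.

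**The concern.** Two adjacent sentences, read together as the trial's sensitivity, use different effects. The reader is given a power figure for one and a raw-scale figure for the other. Both effects also look too small for the sample: a standardized difference near 0.3 usually needs well over 35 per arm, and three measurements correlated at 0.5 reduce the variance of a subject's mean only by a third.

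At stake is how the result will be read. If 85% power for a small effect is taken at face value, a non-significant difference would seem to argue against differences of 2 to 3 PCL points, which the trial is not equipped to exclude.

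**Working it through.** **Inputs** (from the sample-size section): n = 35 per arm, allocation 1:1, two-sided alpha 0.05, target power 85%, m = 3 time points, ICC r at most 0.5, SD 8.1 PCL points, effects 0.3 and 0.35 SD. My assumptions: compound symmetry and no dropout. The article does not say which contrast the power refers to, so several are tried.

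**Step 1, the raw conversion.** 0.35 × 8.1 = 2.835, so 2.8 points is reproduced, for 0.35 SD. For the effect that carries the power claim, 0.3 × 8.1 = 2.43.

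**Step 2, formulas.** With the outcome in SD units, the group difference has SE = √(2·VF/35), where VF is the variance factor:
- mean of m measures: VF = (1 + (m − 1)r)/m
- baseline-adjusted mean of m post-baseline measures: VF = (1 + (m − 1)r)/m − r²
- single time point: VF = 1
- change score: VF = 2(1 − r), which is 1 at r = 0.5

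Power is from the noncentral t distribution with 68 df and noncentrality d/SE.

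**Step 3, the time-averaged contrast at r = 0.5.** VF = (1 + 2 × 0.5)/3 = 0.667; SE = √(2 × 0.667/35) = 0.195; noncentrality at 0.3 SD = 0.3/0.195 = 1.54. Power is 33% at 0.3 SD and 42% at 0.35 SD. Power reaches 85% at d = 0.593, and 0.593 × 8.1 = 4.8 points. At this VF, 85% power would need about 134 per arm for 0.3 SD and 99 for 0.35 SD.

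**Step 4, other readings.**

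| Contrast | VF | Power at 0.3 SD | Power at 0.35 SD | Detectable at 85% (SD) | PCL points |
|---|---|---|---|---|---|
| Mean of three, ICC 0.5 | 0.667 | 33% | 42% | 0.59 | 4.8 |
| Mean of three, ICC 0.25 | 0.500 | 42% | 53% | 0.51 | 4.2 |
| Mean of three, ICC 0 | 0.333 | 57% | 71% | 0.42 | 3.4 |
| Baseline-adjusted, one post, r = 0.5 | 0.750 | 30% | 39% | 0.63 | 5.1 |
| Baseline-adjusted, two post, r = 0.5 | 0.500 | 42% | 53% | 0.51 | 4.2 |
| Baseline-adjusted, three post, r = 0.5 | 0.417 | 48% | 61% | 0.47 | 3.8 |
| Single time point, or change score at r = 0.5 | 1.000 | 24% | 30% | 0.73 | 5.9 |

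The normal approximation gives values about one percentage point higher (for example 34% / 43% in the first row) and changes nothing.

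**Step 5, what does return 85% at 0.3.**
- If 0.3 is Cohen's f in the between-group test of a repeated-measures ANOVA, the noncentrality is 70 × 3 × 0.3²/(1 + 2 × 0.5) = 9.45 and power is 85.8%. For two groups d = 2f; exactly 85% falls at f = 0.297, that is d = 0.593, the same value as in Step 3.
- If between-subject variance is dropped, VF = (1 − 0.5)/3 = 0.167 and power at 0.3 SD is about 86%. This is the Step 3 variance divided by four, so it has the same effect as doubling d.

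**Step 6, the group-by-time test.** Entering f = d/2 directly as the interaction effect gives 78% at d = 0.3 and 90% at d = 0.35. That entry does not represent a group difference of d that emerges after baseline. With actual mean patterns (no difference at baseline and d at the last or the last two times, or a linear build-up to d), power is 18–30% on 2 df and 24–39% on 1 df.

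**The case against.** Five points can be made for the plan.

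**The contrast is not named and the ICC is an upper bound.** This stands. A reader might infer that 0.59 SD is the one detectable effect implied by the stated inputs. The article does not support that: 0.59 belongs to the time-averaged difference at the ICC ceiling, and averaging is not even the plan's best case. Baseline adjustment with two or three post-baseline measures does better at the same correlation. No row of the table reaches 85% at 0.35 SD, however.

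**A flat shortfall would be too strong.** A reader might infer that the raw figure is too small by a factor of about 1.7 and that the chance of detecting such effects is always below one half. The factor is 4.8/2.8 = 1.7 in the first row of the table but 3.4/2.8 = 1.2 at ICC 0. Power at 0.35 SD exceeds one half in four of the seven rows.

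**The metric may simply be mislabelled.** The agreement at f = 0.3 is suggestive but does not show that f was reported as SD units. If it was, the calculation may be sound and the sentence is still wrong, because it states SD units and the true detectable d is then about 0.59.

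**The article does not call 2.8 points detectable.** Correct. It says only that 0.35 SD equals 2.8 points, and that product is right. The detectable reading comes from placing the sentence directly after the power claim. PCL total is also not the primary outcome, which Study aims gives as emotional numbing.

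**This is a pilot, and the Discussion concedes that negative findings will be harder to interpret.** Both soften the consequence. Neither makes a specific power figure correct when its own inputs do not yield it.

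**Conclusion.** The point holds. The two sentences use different effects, 0.3 SD (2.4 points) for power and 0.35 SD for the 2.8 points, and 35 per arm provides 85% power for neither as a between-group difference in SD units. Across the contrasts in the table, power at 0.3 SD is 24–57% and at 0.35 SD 30–71%; the effect detectable at 85% is 0.42 to 0.73 SD (3.4 to 5.9 points). This rests on compound symmetry and full follow-up; dropout would lower power further. It does not establish that the sample should be larger, nor where the 85% came from. The stated sensitivity is wrong and should be corrected before results are interpreted against it.

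**What to change.** Keep 70 participants. Confirm from the original calculation whether 0.3 was d or f, and which contrast and time points it referred to. Then use one effect size in both sentences, name the contrast and the metric, and restate. For example: with 35 per arm, three time points, ICC 0.5, two-sided 0.05 and no dropout, the time-averaged group difference detectable with 85% power is about 0.59 SD (about 4.8 PCL points at SD 8.1); power at 0.3 to 0.35 SD is about 33 to 42%. Add the range for a lower ICC or for baseline adjustment, or replace the example with the row of the table that matches the planned contrast. Do not present 2.8 points as the effect the trial can detect.

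The cost is the rewording of two sentences and a less favourable stated figure. Recruitment, conduct and analysis do not change.
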